### Intervention group

Participants assigned to the intervention group received an e-mail containing the dates of programme updates, the website URL of the intervention programme, a password for browsing the website, and the following information.

The programme updates were sent on Monday morning of each week during the intervention period. Participants received a total of five e-mails on the nutrition education programme over the 5 weeks of the intervention period. On the first occasion, participants received an e-mail containing (1) instructions on how to access the website (i.e. the URL and password), (2) an overview of the programme and how it would proceed, and (3) the programme contents for the first week. The e-mails sent in the subsequent weeks, in addition to item (1–3), included (4) a review of the contents of the previous step. The programme website was made freely accessible only for the duration of the intervention period, and after which it was closed. Participants’ passwords were effective for the duration of the study. If a participant forgot his or her password, it could be retrieved by contacting a research officer. After completion of the 5-week intervention, participants received an e-mailed request to participate in the post-intervention survey (T2). Finally, participants received another e-mail request to participate in a follow-up survey 3 months after completing the intervention (T3).

### Control group

The control group surveys took place over the same period as intervention group surveys. Control group participants received an advance notification e-mail after the baseline from the survey company that another survey would take place 5 weeks later. After a 5-week-long silence, participants received an e-mail request to take part in the post-intervention survey (T2). Subsequently, participants received an e-mail request to participate in a follow-up survey 3 months later (T3).

### Intervention programme

An interactive webpage called the ‘Diet and Exercise Practices Project (http://healthpromotionqol.com)’ is designed to improve vegetable intake of visitors to help decrease the likelihood of lifestyle-related diseases (Fig. 2). It is a free website that provides information, a monitoring sheet, and advice about healthy diets, increasing vegetable intake, and preventing lifestyle-related diseases. We hypothesize that achieving an approximately 70 g (1 serving) increase in vegetable intake might help lower-income groups to catch up while simultaneously contributing to the partial resolution of the deficient vegetable intake amongst Japan’s adult population. Therefore, the action goals of intervention is a vegetable dish to eat five servings, or was a plus 1 serving (approximately 70 g) per day. The programme is divided into five steps that align with the stages of behaviour change. Table 1 shows the framework of the programme. To be updated every week, but watch the past step not proceed in the previous step. It was created to advance the based on behavioural science theory. To avoid contamination during the intervention period, access to the webpage was password-restricted so that only study participants could visit it.

**Fig. 2 Fig2:**
[figure not shown]
A snapshot of the website

**Table. 1 Tab1:** Five steps and accompanying components of the dietary education intervention

Step	Stages of change and message	No	Items	Topics	Practice points (e.g., worksheets)	Behavioral science theory	Behavioral modification technique	Health literacy	Processes of change
1	Precontemplation → Contemplation (Encourage interest in vegetables)	1	Today's points	Eating a lot of vegetables is good for our health		Health belief model	Perceived susceptibility, perceived severity	Seeking information from various sources, Extracting relevant information	Dramatic relief, raising awareness
		2	Do you know?	It is recommended that we consume 350 g of vegetables per day	Points: 350 g of vegetables = 5 servings	Cognitive behavior theory	Cognitive restructuring	Seeking information from various sources, Considering the credibility of the information	Dramatic relief, raising awareness
		3	Easy to devise	Self-check! Counting the number of vegetable dishes	Self-check: How many vegetable dishes (servings) do you eat per day?	Social cognitive theory, theory of planned behavior	Self-monitoring	Considering the credibility of the information	Raising awareness
		4	Let's try it!	Live a healthy life by eating vegetables daily	Worksheet: record the number of vegetable dishes (servings) that you ate daily.	Social cognitive theory, theory of planned behavior	Subjective norm, self-monitoring	Considering the credibility of the information, Making decisions based on the information	Raising awareness
2	Contemplation → Preparation (Try to increase number of vegetable dishes by one (+1))	1	Today's points	You decide your one dish (+1)	Points: Let's choose the “ + 1” with the confidence so we can practice it at home and in restaurants.	Social cognitive theory, theory of planned behavior	Contingency management	Extracting relevant information	Self-reevaluation
		2	Do you know?	At home: Point the convenience easy recipes for your one dish (+1)		Social cognitive theory, theory of planned behavior	Role playing	Seeking information from various sources, Extracting relevant information	Raising awareness, counterconditioning
		3	Easy to devise	Eating out: How to choose simple dishes depending on your one dish (+1)		Social cognitive theory, theory of planned behavior	Role playing	Seeking information from various sources, Extracting relevant information	Raising awareness, counterconditioning
		4	Let's try it!	Let's do so! Eat your one dish (+1) from today onwards	Worksheets: I will try my “ + 1” for today's meal!	Stimulus-response theory, social cognitive theory	Stimulus control, goal setting, self-monitoring	Extracting relevant information, Making decisions based on the information	Self-liberation
3	Contemplation →Preparation (Meals can be opportunities to evaluate one's dietary balance)	1	Today's points	Eat a proper meal based on your confidence in the future of your health	Points: Let's check whether a meal contains everything (i.e., a staple food, a main dish, side dish) or not.	Social cognitive theory, theory of planned behavior	Contingency management, commitment	Extracting relevant information	Self-reevaluation
		2	Do you know?	At home: Tonight's dinner is now OK		Social cognitive theory, theory of planned behavior	Role playing	Seeking information from various sources, Extracting relevant information, Making decisions based on the information	Raising awareness, counterconditioning
		3	Easy to devise	Eating out: balance achieved by combining foods is OK	Try: Let's choose meal that contains a staple food, main dish, side dish when eating out or at a convenience store.	Social cognitive theory, theory of planned behavior	Role playing	Seeking information from various sources, Extracting relevant information, Making decisions based on the information	Raising awareness, counterconditioning
		4	Let's try it!	Challenging your to balance your meal	Work sheets: I practice the goal that this myself decided!	Social cognitive theory, theory of planned behavior	Role playing, commitment, self-monitoring, behavior analysis	Extracting relevant information, Understanding and communicating the information, Making decisions based on the information	Self-liberation
4	Preparation →Action (Precautions for a healthy diet)	1	Today's points	What do you do if you cannot eat?		Social cognitive theory, theory of planned behavior	Contingency management	Seeking information from various sources	Environmental reevaluation
		2	Do you know?	Practical examples: recommended measures		Stimulus-response theory	Stimulus control, counterconditioning	Extracting relevant information, Considering the credibility of the information, Making decisions based on the information	Stimulus control, counterconditioning
		3	Easy to devise	Characteristics of those who are eating plenty of vegetables	Self-check: What precautions do you take? Check each item that applies!	Stimulus-response theory	Counterconditioning, modeling, self-monitoring, behavior analysis	Seeking information from various sources, Considering the credibility of the information, Extracting relevant information	Stimulus control, counterconditioning
		4	Let's try it!	Devise a goal: Let's make precautions for when something does not work	Try: In case eating a “ + 1” does not go well, let's decide on a precaution beforehand.	Stimulus-response theory	Commitment, stimulus control	Extracting relevant information, Considering the credibility of the information, Making decisions based on the information	Stimulus control, self-liberation
5	Action →Maintenance (Healthy community helps us)	1	Today's points	Everyone's goal is to improve their health		Social cognitive theory, theory of planned behavior, social network, social support	Contingency management, self-monitoring	Extracting relevant information, Considering the credibility of the information, Making decisions based on the information	Helping relationships, social liberation
		2	Do you know?	Eat a delicious meal together with family and friends!	Self-check: What kind of topic do you talk about with family and friends?	Social cognitive theory, theory of planned behavior	Subjective norms, self-monitoring	Extracting relevant information, Understanding and communicating the information, Making decisions based on the information	Helping relationships, social liberation
		3	Easy to devise	Investigate safe diets in the community	Try: Let's look for a shop that supports health promotion in your community!	Social cognitive theory, theory of planned behavior	Subjective norms	Seeking information from various sources, Extracting relevant information	Helping relationships, social liberation
		4	Let's try it!	Let's be healthy by eating vegetables! Spend a day having a fun diet	Try: Let's review a past topic! Try: Let's settle on a “ + 1” that you can begin introducing to family and friends! Free description: Questions and free comments	Social cognitive theory, theory of planned behavior	Commitment, self-monitoring, contingency management	Extracting relevant information, Considering the credibility of the information, Understanding and communicating the information, Making decisions based on the information	Social liberation

In order to achieve this action goals were designed following the intervention programme. To encourage behavioural changes, the programme contents are prepared using behavioural theories and techniques tailored to the individual stages of behavioural change. In the first step, we employ the health belief model to encourage a shift from the pre-contemplative to the contemplative phase; in the second and third steps, social cognitive theory is used to encourage transition to the preparatory phase; in the fourth step, social cognitive theory and strengthening social support are used to promote progression to the execution phase; finally, in the fifth step, strengthening social capital and social support are used to promote the shift to the maintenance phase. All of the steps is composed of four items, as introducing “Today's point (Including review of the previous week from the second week onwards)”, information and skills necessary to behaviour modification as practical content “Do you know?” and “Easy in devising” are on two page, as summary “Let's try it !(to support behaviour change by using a work sheet)”.

### Web design

The website design was settled on through consultations with registered dieticians, health movement educator, and public health experts. Regarding the size of the online text, the amount of information, and the configuration of the website, we obtained the advice of web design professionals. Figures 2 and 3 show a snapshot on programme of the website, while the website structure is shown in Fig. 4.

**Fig. 3 Fig3:**
[figure not shown]
A snapshot on programme page of the website

**Fig. 4 Fig4:**
[figure not shown]
Website structure

### Assessment

The primary outcome variable was assessed using a self-administered questionnaire in Japanese. Regarding the assessment, at baseline (T1), primary outcomes, transtheoretical model [31], self-efficacy [32], dietary knowledge [33], perceptions of neighborhood food environments within secondary outcomes, and all other measurements. After completion of the 5-week intervention, participants received an e-mailed request to participate in the post-intervention survey (T2). At post-intervention survey (T2), we assessed the all primary outcomes, all secondary outcomes, all other measurements excluding the subjective economic status. We evaluated about the participants’ satisfaction of process evaluation as after intervention. Finally, participants received another e-mail request to participate in a follow-up survey 3 months after completing the intervention (T3). At follow-up survey (T3), we assessed the all primary outcomes, all secondary outcomes, and all other measurements excluding the subjective economic status.

### Primary outcomes

As Health Japan 21 (the secondterm﻿), it is necessary to evaluate the intervention that applies to the improvement of diet-related quality of life. Interventions that focus on dietary lifestyle require evaluation of diet-related quality of life as primary outcomes. Two of the subscales of the Subjective Diet-Related quality of life scale includes dietary satisfaction and fun of meals. As primary outcomes, we considered Subjective Diet-Related quality of life, which comprised an assessment of the final dieting goal (2 items) [34], and self rated health, which has been reported to be associated with both socio-economic status and mortality [35, 36].

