### Statistical analyses

All statistical analyses will be performed with IBM SPSS Statistics 21.0. For continuous variables, independent t-tests will be used to determine inter-group differences and Man–Whitney U-tests for intra-group comparison, while the χ^2^ or an equivalent test is to be used to determine the associations between categorical variables. Because this is a prospective RCT involving repeated measures, repeated measures analyses of variance will be applied to determine significant differences within the study groups. We also considered the possible effect of time on groups. The evaluation of the intervention is based on an intention-to-treat analysis. A *p*-value of 0.05 has been set as the level of significance.

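### Two primary outcomes are measured at two visits under a single 0.05 level, with no primary visit, hierarchy or success rule fixed

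*Protocol article*

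**What the plan says.** All references are to the protocol article.

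- **Primary outcomes.** The section states "As primary outcomes, we considered Subjective Diet-Related quality of life, which comprised an assessment of the final dieting goal (2 items"), and continues "and self rated health, which has been reported to be associated with both socio-economic status and mortality". It also says "Two of the subscales of the Subjective Diet-Related quality of life scale includes dietary satisfaction and fun of meals". It does not say whether the two items form one score or two.
- **Assessment.** "At post-intervention survey (T2), we assessed the all primary outcomes", and then "At follow-up survey (T3), we assessed the all primary outcomes". Neither visit is called primary.
- **Statistical analyses.** For continuous variables, "independent t-tests will be used to determine inter-group differences". Repeated measures ANOVA is planned for differences within the groups, and a further sentence mentions an effect of time on groups. On the error rate, the section says only that a p-"value of 0.05 has been set as the level of significance".
- **Sample size.** One effect size (0.5), one alpha (0.05) and one power (0.95) are given, tied to no outcome and no visit.

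**The concern.** T2 and T3 answer different questions: the effect at the end of the programme, and whether it lasts 3 months. As written, either visit on either outcome could be presented as the primary result. An effect that has faded by T3, or a chance difference seen only at T3, would each qualify. Choosing the visit or outcome after seeing the data would then make a false primary finding more likely than the 0.05 attached to each test suggests.

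This is separate from the disagreement between the Abstract, which gives vegetable eating as the main outcome, and Methods, where it is secondary. Whichever outcome is primary, two visits still compete.

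**Working it through.** The article gives no trial-wide error rate to reproduce. Its 0.05 is a level per test, taken here as two-sided because sidedness is not stated.

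**Inputs.** Two primary outcomes, or three scores if the two quality-of-life items are kept apart (Primary outcomes). Two post-baseline visits (Assessment). Level 0.05 (Statistical analyses). The article gives no correlations, so these are assumed: 0 to 0.7 between outcomes and 0 to 0.8 between T2 and T3.

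**Formulas.** For m independent tests, the chance of at least one false positive is 1 − 0.95^m. The ceiling under any dependence is m × 0.05. For correlated tests, 1,000,000 sets of normal test statistics were simulated for each pair of assumed correlations.

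| Reading | Tests | Independent | Ceiling | Over assumed correlations |
|---|---|---|---|---|
| 2 outcomes × 2 visits | 4 | 1 − 0.95^4 = 0.185 | 0.20 | 0.127 to 0.186 |
| 3 scores × 2 visits | 6 | 1 − 0.95^6 = 0.265 | 0.30 | 0.166 to 0.265 |
| 2 outcomes, one group-by-time test each | 2 | 1 − 0.95^2 = 0.0975 | 0.10 | not simulated |
| 3 scores, one group-by-time test each | 3 | 1 − 0.95^3 = 0.143 | 0.15 | not simulated |

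The top of each simulated range is the zero-correlation case, so it equals the independent figure apart from simulation error.

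As multiples of 0.05, four tests give 0.127/0.05 = 2.5 to 0.185/0.05 = 3.7. Six tests give 0.166/0.05 = 3.3 to 0.265/0.05 = 5.3. A single outcome tested at both visits gives 0.084 to 0.091 at visit correlations of 0.5 to 0.7, or about 1.7 to 1.8 times.

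These figures count false positives in either direction. Counting only differences that favour the programme, four tests give 0.063 to 0.096 against 0.025, or 2.5 to 3.8 times. The relative inflation is almost the same.

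**Can the sample carry a correction?** Expected completers are 900 × (1 − 2/3) = 300 and 600 × (1 − 1/2) = 300 (Sample size). At effect size 0.5 and 95% power, 105 per arm are needed at 0.05, and 123 at 0.025, the stricter Holm step for two outcomes. With 300 per arm, power exceeds 0.999 even at 0.05/6. The smallest effect detectable with 95% power rises from (1.960 + 1.645) × √(2/300) = 0.294 SD to (2.241 + 1.645) × √(2/300) = 0.317 SD.

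The stated sample-size inputs do not reproduce 900 and 600. They give 315 and 210 after dropout, or 630 and 420 with two income strata. The planned sample is larger than either, and nothing here depends on the difference.

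**The case against.** The strongest reply is that multiplicity rules are commonly left to an analysis plan, which is not shown, and that this is a condensed article. That holds for the choice of correction. It does not dispose of the point, because the article itself defines the primary outcomes, their visits and the significance level, and what it defines leaves the primary comparison open.

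Four further replies limit the size or the remedy:

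- **Longitudinal analysis.** The sentence on time and groups may mean one group-by-time test per outcome. If so, the visits do not compete and the figure is about 10%. The wording is unclear, since between-group differences are assigned to t-tests, so both readings must be carried.
- **Success rule.** If every primary outcome had to be positive, there would be no inflation. No rule is stated either way.
- **Five-fold inflation.** A reader might infer this from two outcomes and two visits. Four tests at 0.05 cannot exceed 0.20, which is four times. Five is reached only if the two quality-of-life items are tested separately, which the article neither states nor rules out.
- **The visits.** A reader might take T2 as measured while the website is still open and T3 as measured after it has closed. The Intervention group section does not support this: the site closes at the end of the intervention period, and the T2 request follows completion. Nor does the article dictate T2 as primary. The main objective in Background concerns the effects of a 5-week programme without saying when, and the fifth step, aimed at maintenance, could argue for T3.

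**Conclusion.** The point holds in a conditional form. Two primary outcomes, two visits and one 0.05 level are fixed, while the primary visit, the ranking of the outcomes and the success rule are not. If visits are tested separately and any one positive result counts, the chance of at least one false positive primary result is about 13% to 19%. It is up to about 26% if the two quality-of-life items are separate tests, and about 10% with one group-by-time test per outcome. The ranges rest on assumed correlations and two-sided tests.

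It would be wrong to say that the article promises a trial-wide 0.05 and breaks it. It sets a level of significance and makes no claim about the overall rate. The defect is that the primary comparison is left open, not that a stated error rate is false.

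**What to change.** In Assessment, Primary outcomes and Statistical analyses, before any outcome comparison is run:

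1. Name one primary visit and make the other secondary. T2, the end of the 5-week programme, fits the main objective in Background. The choice is the sponsor's, but it must be made in advance.
2. State that the two diet-related quality-of-life items are scored as one measure.
3. Either keep one primary outcome or, if both are kept, test them at the primary visit with Holm at an overall 0.05: the smaller p-value against 0.025 and, if that passes, the other against 0.05.
4. State which between-group test gives the primary result.

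This needs no new data. The costs are that an effect seen only at the other visit becomes a secondary finding, and that with two primary outcomes the first must pass a stricter threshold. At the planned effect size of 0.5 the expected 300 completers per arm absorb this. If the true effect is much smaller, or fewer participants complete, the loss of power would be greater.

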**Methods/Design:**

Participants will be randomly sampled individuals (aged 30–59) stratified according national population statistics for sex, age, and household income. Participants were consented to survey participation (*n* = 1500), and will be randomly divided into intervention and control groups. The intervention period is 5 weeks with one step of diet-related education per week. The main outcome of the programme is dietary behaviour as eating vegetable (350 g per day, five small bowl). To encourage behavioural changes, the programme contents are prepared using behavioural theories and techniques tailored to the assumed group stages of behavioural change. In the first step, we employ the health belief model to encourage a shift from the pre-contemplative to the contemplative phase; in the second and third steps, social cognitive theory is used to encourage transition to the preparatory phase; in the fourth step, social cognitive theory and strengthening social support are used to promote progression to the execution phase; finally, in the fifth step, strengthening social capital and social support are used to promote the shift to the maintenance phase. The baseline, post intervention and follow-up survey was assessed using a self-administered questionnaire. For process evaluation, we use five items relating to programme participation and satisfaction. A follow-up survey of participants will be carried out 3 months after intervention completion.

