In Japan, Ministry of Internal Affairs and Communications report on Internet usage by Japanese citizens [25] shows that, today, the proportion of Internet users among all Japanese aged 30–59 is 90% or more. Furthermore, the proportion of lower-income individuals (i.e., who are earning less than two million JPY per annum; approx. 15,800 GBP) is 61%, and rising annually. A relatively high proportion of respondents to this report indicated that they use the Internet to search for information about health and medicine, ranging from 73% among 30-year-olds to 80% among 59-year-olds. The proportion of respondents who reported using the Internet at least once a week was as high as 91%. Thus, as a form of information and communications technology (ICT), the Internet is a powerful health education tool for which future expansion can be anticipated in fields of health promotion, especially nutrition [26]. Web-based nutrition education programmes by their nature rely on ICT and the Internet in particular [27]. However, in the context of web-based support for increased vegetable intake, there are almost no reports, even at the worldwide level, verifying the effects of these programmes according to income level.

In this paper, we describe the methods and protocol of a randomized controlled trial (RCT) that seeks to verify the effectiveness of a web-based nutrition education programme of promoting vegetable intake among adults and that is based on behavioural science theory. The main objective of the RCT is to develop and verify the effects of a 5-week programme of promoting vegetable intake. A secondary objective is to determine how the effects of this web-based nutrition education programme differ according to socio-economic status.

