### Secondary outcomes

The secondary outcomes were eating behaviours, which was considered an index of behavioural change and is often held up as the goal of nutrition education. Three eating behaviours (per week) were considered: mealtime balance, or eating ‘balanced meals comprising a staple food, a main dish, and a side dish’ [37], ‘eating dark green vegetables’, and ‘eating full servings of vegetables (5 small dishes or approx. 350 g per diem)’ [38]. The mealtime balance behaviour has been shown to facilitate nutrient intake and improve nutritional status [39–41]. To explain the staple foods, main dishes, side dishes, and vegetable servings, we posted sample photographs for reference in terms of size and amount, and stipulated that respondents should always check these photographs before responding. Because daily eating behaviours (two items) were checked using these photographs depicting single (70 g) servings of vegetables, participants were also asked to answer how many vegetable servings they consumed per diem. This item reflects the fact that, as demonstrated by Ozawa et al. [42], the behavioural goal of ‘five or six small [vegetable] dishes a day’ can potentially serve as an easily grasped indicator of consuming 350 g per diem. Additionally, the amount of vegetables eaten each day (in g) was also self-reported.

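### The article does not identify one primary outcome that answers its own objective: vegetable eating is the main outcome in the abstract but secondary in the Methods

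*Protocol article*

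**What the plan says.** The abstract (Methods/Design) states: "The main outcome of the programme is dietary behaviour as eating vegetable (350 g per day, five small bowl". It names no other outcome apart from the process evaluation.

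The end of the Background gives the purpose: "The main objective of the RCT is to develop and verify the effects of a 5-week programme of promoting vegetable intake". The hypothesis, in the Background and again under Intervention programme, is a gain of about 70 g (one serving). The intervention's target is worded the same way: "the action goals of intervention is a vegetable dish to eat five servings, or was a plus 1 serving (approximately 70 g) per day".

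The Methods rank the outcomes differently. Under Primary outcomes: "As primary outcomes, we considered Subjective Diet-Related quality of life", a two-item measure, "and self rated health, which has been reported to be associated with both socio-economic status and mortality". Under Secondary outcomes: "The secondary outcomes were eating behaviours, which was considered an index of behavioural change", and one of the three behaviours listed there is "eating full servings of vegetables (5 small dishes or approx. 350 g per diem". Servings per day and self-reported grams per day appear in the same section. Other measurements again treats the eating behaviours as secondary.

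The Sample size section gives an effect size, alpha and power without an outcome. The Statistical analyses section says only "A *p*-value of 0.05 has been set as the level of significance", without naming an endpoint or a time point.

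**The concern.** The abstract and the Methods give different answers to the question of which result decides the trial. The objective and hypothesis side with the abstract. Under the Methods, neither primary outcome measures vegetable intake, so a positive primary result would not show that intake rose, and a gain of one serving per day would be only a secondary finding.

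Choosing the Methods over the abstract still does not leave a single endpoint. Assessment opens by speaking of one primary outcome variable, whereas Primary outcomes names two, both measured after the intervention (T2) and at 3 months (T3).

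The ranking also affects what is known to be measured. Assessment lists the primary outcomes at baseline (T1), then four psychosocial and environmental measures, then the other measurements. It does not name the eating behaviours. If vegetable eating is primary, its baseline is covered. If it is secondary, its baseline is not clearly listed, which matters for a repeated-measures analysis.

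**Working it through.** **1. The passages side by side**

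| Place in the article | Vegetable eating | Diet-related quality of life, self-rated health |
|---|---|---|
| Abstract, Methods/Design | main outcome | not mentioned |
| Background, objective and hypothesis | the target (+70 g, one serving) | not mentioned |
| Intervention programme, action goal | the target (five servings or +1) | not mentioned |
| Primary outcomes | not mentioned | primary |
| Secondary outcomes; Other measurements | secondary | not mentioned |
| Sample size; Statistical analyses | not mentioned | not mentioned |

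The vegetable item is the same in both places: 350 g per day, as five small bowls or dishes. This is one variable with two ranks, not two variables with similar names.

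**2. Does the sample size reveal the intended outcome?**

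Inputs (Sample size): effect size 0.5, alpha 0.05, power 0.95, dropout two-thirds (intervention) and one-half (control), 900 and 600 enrolled.

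- A two-sided two-sample t-test with d = 0.5 needs 105 evaluable per arm. With the stated dropout that is 105 / (1 − 2/3) = 315 and 105 / (1 − 1/2) = 210.
- The stated sizes leave 900 × 1/3 = 300 and 600 × 1/2 = 300 completers. The calculation does not reproduce 900 and 600. That is a separate matter, since the planned number exceeds what these inputs need.
- A standardised effect of 0.5 fits any continuous outcome. If it were meant for the 70 g hypothesis, it would imply a standard deviation of 70 / 0.5 = 140 g, but the article gives no standard deviation.

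So the sample size does not settle which outcome is primary.

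**3. Error rate if the two Methods outcomes remain primary**

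Assumptions: one two-sided test per outcome at 0.05, and success on either is enough.

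- Independent tests: 1 − (1 − 0.05)² = 0.0975, or 9.75%.
- Correlated tests (correlation assumed, by simulation): 9.5% at 0.3, 9.1% at 0.5, 8.3% at 0.7.
- If both outcomes had to succeed, the rate would not exceed 5%. The article does not say which rule applies.

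**4. What a multiplicity rule would cost**

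Bonferroni for two outcomes uses 0.05 / 2 = 0.025. With d = 0.5 and 95% power this needs 123 evaluable per arm, against 300 expected completers. Power is no obstacle.

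**The case against.** The Methods are consistent among themselves: they set out primary outcomes, then secondary outcomes, and then refer back to eating behaviours as secondary. They also argue for diet-related quality of life from national health policy, so its rank is a reasoned choice. The abstract speaks of the main outcome of the programme, which could mean the behaviour being taught, and the objective refers to the programme's effects without saying which ones.

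Part of this stands. The Methods ranking is deliberate, and preferring quality of life is not in itself an error. The conflict remains, because the abstract's sentence describes the trial's design and the outcome it names is ranked secondary in the Methods.

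Three stronger readings are tempting and are not supported:

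- A reader might count two quality-of-life items and self-rated health at two time points as six tests, with an error rate near 26% (1 − 0.95⁶ = 0.265). The article does not say that the items are tested separately, and it plans a repeated-measures analysis rather than separate tests at T2 and T3.
- A reader might infer that no adjustment is planned, or that the investigators mean to pick whichever outcome succeeds. The article is only silent on adjustment, and a full protocol, analysis plan or the registration may settle both.
- A reader might argue from the programme's name. The website is called the Diet and Exercise Practices Project, which does not mention vegetables.

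**Conclusion.** The contradiction is explicit in the current text. The abstract's main outcome is a secondary outcome in the Methods, the objective and hypothesis follow the abstract, and neither the sample size nor the analysis section decides between them. As written, the article does not identify one primary outcome that answers its own objective, and this determines what the trial can conclude.

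The error-rate consequence is modest and conditional: up to 9.75% for the two Methods outcomes, less if they are correlated, and only if either one counts as success. The main point rests on comparing the passages and does not depend on that figure.

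**What to change.** Before outcome data are analysed, and consistent with the registration, make the abstract, Assessment, Primary outcomes and Secondary outcomes name the same primary outcome and time point, and state that the effect size of 0.5 refers to it. Either of two routes is coherent:

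- **Vegetable intake as primary.** One of the measures under Secondary outcomes (frequency of eating full servings, servings per day, or grams per day) would match the objective. First confirm that it was collected at T1. The documents do not dictate which measure, or whether T2 or T3.
- **Quality of life and self-rated health as primary.** Correct the abstract, limit the primary conclusion to these outcomes, and state whether either or both must succeed. If either suffices, give a multiplicity rule such as Bonferroni or Holm.

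The cost is mainly wording, plus the check on baseline collection. The downside is that whichever outcomes are not chosen lose primary status. Timing matters because much of the article describes allocation and assessment in the past tense. A change made after outcomes have been examined would itself be a post hoc switch.
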